#### **6.3.5.1 Daratumumab SC Dosing**

Daratumumab SC injection will be administered as follows:

- Cycles 1-2: Days 1, 8, 15, 22
- Cycles 3-8: Days 1, 15
- Cycles 9-24: Day 1

All daratumumab administrations will be in an outpatient setting. Subjects will receive concomitant medications as outlined in [Section 6.2.2](#).

Vital signs should be monitored extensively on Cycle 1 Day 1 before, and after the first administration of daratumumab. For all other administrations, vital signs should be measured before the start of injection and at the end of the injection. If the subject experiences any significant medical event, then the investigator should assess whether the subject should stay overnight for observation. If the subject has not experienced a significant medical event but is hospitalized overnight only for observation, then the hospitalization should not be reported as an SAE.

If an infusion-related reaction (IRR) develops, then the injection should be temporarily interrupted or slowed down. In the event of a life-threatening IRR (which may include pulmonary or cardiac events) or anaphylactic reaction, dara-SC should be discontinued, and no additional dara-SC should be administered to the participant. See Section 6.5.1 for instructions on the management of IRRs.

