## 6.5 Dose-modification guidelines

The following sections and tables summarize dosing modifications of daratumumab, carfilzomib, lenalidomide and dexamethasone to manage possible toxicity. Dose modifications different from those stated in the protocol should be discussed with the Lead Principal Investigator. Administration of daratumumab, carfilzomib and lenalidomide will be discontinued in the event of any other toxicity that, in the opinion of the lead, secondary site, or treating investigator, warrants discontinuation.

In addition to dose reductions, administration of daratumumab, carfilzomib and lenalidomide will be held temporarily in the event of a treatment-related toxicity at the treating investigator's discretion.

Study treatment may be reintroduced if resolution of the event to the baseline value or to  $\leq$  Grade 1 within 21 days; otherwise study drug will be permanently discontinued. Any deviations from this plan must be approved by the Lead Principal Investigator.

All clinically-significant non-hematologic toxicities must be resolved to Grade 1 or baseline.

Individual dose modification of daratumumab is not permitted. Dosing can be delayed to manage daratumumab-related toxicities. Dose de-escalation of daratumumab will be based only on the Data and Safety Monitoring Board (DSMB) recommendation. Dose reduction levels of carfilzomib, lenalidomide and dexamethasone for toxicity management of individual subjects are provided below:

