#### **Injection Site Reactions:**

In clinical studies, SC administration of daratumumab was associated with local injection site reactions, such as induration and erythema, in some subjects. The reactions usually resolved within 60 minutes. Local injection-site reactions should be managed per institutional standards.

Individual dose modification of Dara SC is not permitted. For managing Dara SC-related toxicities, either a dose interruption or a dose delay is recommended.

Daratumumab must be held if any of the following criteria below are met, to allow for recovery from toxicity, regardless of relationship to daratumumab:

- Grade 4 hematologic toxicity, except for Grade 4 lymphopenia;
- Grade 3 or higher thrombocytopenia;
- Febrile neutropenia;
- Neutropenia with infection, of any grade;
- Grade 3 or higher non-hematologic toxicities with the following exceptions:
  - Grade 3 nausea that responds to antiemetic treatment within 7 days
  - Grade 3 vomiting that responds to antiemetic treatment within 7 days
  - Grade 3 diarrhea that responds to antidiarrheal treatment within 7 days
  - Grade 3 fatigue that was present at baseline or that lasts for <7 days after the last administration of daratumumab
  - Grade 3 asthenia that was present at baseline or that lasts for <7 days after the last administration of daratumumab

Other than on Day 1 of a cycle, if any ‘within-cycle’ daratumumab and hyaluronidase-fihj administration does not commence within the prespecified window (see table 6-5 below) of the scheduled administration date then the dose will be considered a missed dose.. Administration may resume at the next planned dose date. A missed dose will not be made up.

Delay of Day 1 drug dosing in any given cycle should not result in a skipped dose but should lead to a delay of the entire cycle instead. A minimum of 4 days between daratumumab doses

must be observed. If a dose is delayed, then the dates of all subsequent doses must be adjusted. If a dose delay occurs, then blood samples should be collected on the actual day of study drug administration, not on the original scheduled drug administration day.

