**Table 6-5 Daratumumab Administration Window**

| Cycles  | Frequency             | Dose Held | Dosing Re-start                        |
|---------|-----------------------|-----------|----------------------------------------|
| 1 and 2 | Weekly (q1wk)         | >3 days   | next planned weekly dosing date        |
| 3 to 6  | Biweekly (q2wks)      | >7 days   | next planned biweekly dosing date      |
| 7+      | Every 4 weeks (q4wks) | >7 days   | next planned every 4 weeks dosing date |

If a dose is delayed, then the dates of all subsequent doses must be adjusted. Any dose hold of more than 14 days due to toxicity will result in permanent discontinuation of daratumumab. Dose holds of more than 14 days for other reasons should be discussed with the Lead Principal Investigator. If a dose delay occurs, then pharmacokinetic and pharmacodynamic assessments should be performed on the actual day of study drug administration, not on the original scheduled administration day.

For infusion-related reactions of any grade/severity, immediately interrupt the daratumumab infusion and manage symptoms. Management of infusion reactions may further require reduction in the rate of infusion, or treatment discontinuation of daratumumab as outlined below:

- Grade 1-2 (mild to moderate): Once reaction symptoms resolve, resume the infusion at no more than half the rate at which the reaction occurred. If the patient does not experience any further reaction symptoms, infusion rate escalation may resume at increments and intervals as appropriate ([Table 6-1](#)).
- Grade 3 (severe): If the intensity of the reaction decreases to Grade 2 or lower, consider restarting the infusion at no more than half the rate at which the reaction occurred. If the patient does not experience additional symptoms, resume infusion rate escalation at increments and intervals as outlined in [Table 6-1](#). Repeat the procedure above in the event of recurrence of Grade 3 symptoms. Permanently discontinue daratumumab upon the third occurrence of a Grade 3 or greater infusion reaction.

- Grade 4 (life threatening): Permanently discontinue daratumumab treatment.

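### The daratumumab hold rules conflict: a toxicity hold of 15 to 21 days can mean reintroduction or a permanent stop, and Table 6-5 disagrees with the Day 1 delay rule and the dosing schedule

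*Protocol*

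**What the plan says.** Four sets of rules in the protocol bear on a held daratumumab dose.

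- **Permanent stop.** Under Table 6-5: "Any dose hold of more than 14 days due to toxicity will result in permanent discontinuation of daratumumab". Holds of that length for other reasons go to the Lead Principal Investigator.
- **General toxicity rule.** Section 6.5 names daratumumab, carfilzomib and lenalidomide as held temporarily for treatment-related toxicity. It then allows study treatment to be reintroduced if the event resolves to baseline or Grade 1 or lower within 21 days; "otherwise study drug will be permanently discontinued". Sections 6.4 and 6.6 also use 21 days, for delay of a new cycle and delay of treatment.
- **Late doses.** In Section 6.5.1.1 the missed-dose window opens with the limit "Other than on Day 1 of a cycle, if any" and so covers within-cycle doses only. A Day 1 delay "should not result in a skipped dose but should lead to a delay of the entire cycle instead". Table 6-5 then gives restart dates by row. A biweekly dose held more than 7 days goes to the "next planned biweekly dosing date". A 4-weekly dose held more than 7 days goes to the "next planned every 4 weeks dosing date".
- **Schedule.** Section 6.3.5.1 has "Cycles 3-8: Days 1, 15" and Day 1 only in Cycles 9-24. The synopsis and Appendix 8 agree. Table 6-5 labels Cycles 3 to 6 biweekly and Cycle 7 onward 4-weekly.

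**The concern.** These are operative restart and stopping rules for the drug whose addition to KRd is under test. If two sentences give opposite instructions for the same toxicity, two sites can both follow the protocol and treat the same patient differently: one resumes daratumumab, the other ends it for good. Exposure, discontinuation counts and safety data would then partly reflect which sentence was read. The 14-versus-21-day conflict can arise before the Cycle 8 response and MRD assessment as well as after it. In a trial of 45 patients, a few such cases would be visible in the results.

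**Working it through.** The plan has no figure to reproduce; the check is a day count on its own rules.

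**Inputs.** Dosing intervals of 7, 14 and 28 days; Table 6-5 windows of more than 3, 7 and 7 days; the 14-day limit under Table 6-5; the 21-day limit in Section 6.5. Day 0 is the date the held dose was due, and I assume both limits run from that day.

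**Formula.** If the toxicity lasts longer than the window, the restart day under Table 6-5 is the smallest multiple of the dosing interval that is not less than the days of toxicity. Otherwise the dose is given on resolution.

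| Row | Days of toxicity | Restart day under Table 6-5 | Over 14, counted to resolution | Over 14, counted to next dose |
|---|---|---|---|---|
| Weekly | 8 | 14 | no | no |
| Weekly | 14 | 14 | no | no |
| Weekly | 15 | 21 | yes | yes |
| Weekly | 21 | 21 | yes | yes |
| Biweekly | 8 | 14 | no | no |
| Biweekly | 14 | 14 | no | no |
| Biweekly | 15 | 28 | yes | yes |
| Biweekly | 21 | 28 | yes | yes |
| 4-weekly | 8 | 28 | no | yes |
| 4-weekly | 14 | 28 | no | yes |
| 4-weekly | 15 | 28 | yes | yes |
| 4-weekly | 21 | 28 | yes | yes |

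**1. Toxicity of 15 to 21 days.** Every row exceeds 14 days under either count, so the Table 6-5 text ends daratumumab. Resolution by day 21 meets the Section 6.5 condition for reintroduction. The conflict holds in all dosing phases and does not depend on how a hold is counted.

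**2. Delay or skip in the 4-weekly phase.** In Cycles 9-24 Day 1 is the only daratumumab dose. The 4-weekly row can there concern only doses that Section 6.5.1.1 excludes from the window. For 8 days of toxicity, the Day 1 rule gives the dose on day 8 and shifts the cycle; the row gives it on day 28. Both cannot be followed.

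**3. Cycle bands.** Table 6-5 places Cycles 7-8 in the 4-weekly row, while the schedule has them biweekly. The practical effect on a held Day 15 dose is small. The next Day 1 falls 29 - 15 = 14 days later, which is not more than 14, and both rows have the same 7-day trigger.

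**4. Counting a hold.** The two counts part only in the 4-weekly row, for toxicity of 8 to 14 days. Counted to resolution, the length is at most 14 and daratumumab continues. Counted to the next dose, it is 28 and the permanent stop applies. The protocol does not say which count is meant.

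**The case against.** The best defence of the 14-day rule is that it is specific to daratumumab while Section 6.5 is general and permissive, and a specific rule is ordinarily read as overriding a general one. Sections 6.4 and 6.6 govern the start of a cycle and the patient's treatment as a whole; a cycle can start without daratumumab, so their 21 days need not compete. This narrows the direct conflict to Section 6.5 against the Table 6-5 text. It does not remove it: Section 6.5 names daratumumab, and no sentence says that the 14-day limit overrides.

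On late doses, the limitation to doses other than Day 1 can be said to displace the 4-weekly row, leaving it merely redundant in Cycles 9-24. That is a fair reading, but a site that consults the table finds a live instruction to the contrary.

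The Lead Principal Investigator approves deviations from the Section 6.5 plan and is to be contacted about an impending discontinuation of a subject. Many doubtful cases would therefore reach one person, which limits divergence between sites. It does not settle what the rule is.

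A reader might infer more: that an 8-day hold ends daratumumab, or that the 4-weekly row can never be used after toxicity without a permanent stop. The documents do not support either. Both need the row applied to a Day 1 dose that the text excludes, and a count to the next dose that the protocol does not adopt. A reader might also infer a loss of doses before the Cycle 8 endpoint from the band labels. That does not follow: Table 6-5 governs held doses and is not a schedule, and a held Day 15 dose in Cycles 7-8 restarts only 14 days later.

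**Conclusion.** The rules are inconsistent as written and need reconciling. The firm conflict is the 15 to 21 day toxicity hold: permanent discontinuation by one sentence, permitted reintroduction by another, in every dosing phase. It assumes only that both limits run from the due date of the held dose. The contradiction between the 4-weekly row and the Day 1 delay rule, and the mislabelled cycle bands, are also on the page.

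The 8 to 14 day case is conditional on applying the 4-weekly row and counting the hold to the next dose. It does not arise in the weekly or biweekly rows, and on the stated schedule it falls after the Cycle 8 endpoint, so it bears on later exposure, safety and durability of response. Its worst case for one patient is a hold at Cycle 9 Day 1: 24 - 9 + 1 = 16 doses.

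For the trial as a whole no size can be given, because the protocol states no expected frequency of such holds.

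**What to change.** Amend the text so that each held dose has one outcome:

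- Reconcile Sections 6.3.5.1, 6.4, 6.5, 6.5.1.1 (with Table 6-5 and the text beneath it) and 6.6.
- State which limit governs daratumumab after toxicity: either make the limits agree, or say expressly that daratumumab has its own.
- Make the 4-weekly row of Table 6-5 and the Day 1 delay rule agree.
- Align the cycle bands in Table 6-5 with the dosing schedule.
- Define whether a hold is counted to resolution of the toxicity or to the next dose given.

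Which limit and which restart rule are right is for the sponsor's clinical leads. The cost is a correction to one table and a few sentences in an amendment, plus notice to sites; sample size and analysis are unaffected.

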#### **Infusion-related Reactions Grade 3 or Higher:**

For IRR AEs (other than laryngeal edema or bronchospasm) that are Grade 3, the Dara-SC administration must be stopped, and the participant must be observed carefully until resolution of the AE or until the intensity of the event decreases to Grade 1, at which point the Dara-SC administration may be restarted at the investigator's discretion. Refer to the USPI for further details regarding continuation of Dara-SC administration.

If the intensity of the AE returns to Grade 3 after restart of the Dara-SC administration, then the participant must be permanently discontinued from Dara-SC treatment.

For IRR AEs that are Grade 4, the Dara-SC administration must be stopped, and the participant permanently discontinued from Dara-SC treatment.

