#### **Recurrent Infusion-related Reactions:**

If a Grade 3 IRR (or Grade 2 or higher event of laryngeal edema, or a Grade 2 or higher event of bronchospasm) recurs during or within 24 hours after a subsequent Dara-SC administration, the participant must be permanently discontinued from Dara-SC treatment.

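### Section 6.5.1.1 keeps an unlabelled procedure from withdrawn IV daratumumab dosing that contradicts the subcutaneous rules on restart and permanent stop after a Grade 3 reaction

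*Protocol*

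**What the plan says.** The heading of Section 6.3.4 states that IV daratumumab is no longer available once version 7, dated February 20, 2023, is approved. Section 6.3.5 gives the route now in use: a fixed 1800 mg subcutaneous dose by manual push. Section 6.3.5.1 then deals with reactions to that injection: "If an infusion-related reaction (IRR) develops, then the injection should be temporarily interrupted or slowed down". It directs the reader onward: "See Section 6.5.1 for instructions on the management of IRRs".

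Section 6.5.1.1 first sets out the subcutaneous rules. For Grade 3 reactions other than laryngeal edema or bronchospasm, the dose is stopped and the patient observed until resolution or "until the intensity of the event decreases to Grade 1, at which point the Dara-SC administration may be restarted". The next rule reads: "If the intensity of the AE returns to Grade 3 after restart of the Dara-SC administration, then the participant must be permanently discontinued". Under the heading on recurrent reactions, if a Grade 3 reaction "recurs during or within 24 hours after a subsequent Dara-SC administration, the participant must be permanently discontinued from Dara-SC treatment".

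The same section continues with the dose-hold criteria, Table 6-5 and a further paragraph with three bullets on infusion-related reactions of every grade. The Grade 3 bullet says: "If the intensity of the reaction decreases to Grade 2 or lower, consider restarting the infusion at no more than half the rate". It goes on: "Repeat the procedure above in the event of recurrence of Grade 3 symptoms". It ends with the stop rule: "Permanently discontinue daratumumab upon the third occurrence of a Grade 3 or greater infusion reaction".

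**The concern.** A site managing a Grade 3 reaction finds two different answers under one section number: when the drug may be restarted, and how many such reactions lead to permanent discontinuation. Both differences run in the less cautious direction. If the later block were followed for a subcutaneous patient, the drug could be restarted one grade earlier, and a second Grade 3 reaction would lead back to the restart procedure where the subcutaneous text requires a permanent stop. Sites could also handle the same event differently. What is at stake is patient safety and uniform conduct; the sCR and MRD analysis does not depend on it.

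**Working it through.** No arithmetic beyond a count applies, so the check sets the texts side by side.

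**Step 1: the route in force.** Sections 6.3.4 and 6.3.5 together leave subcutaneous dosing as the only route. Any daratumumab reaction rule used under this version is therefore used on a subcutaneous patient.

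**Step 2: the two Grade 3 procedures in Section 6.5.1.1.**

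| Point | Subcutaneous rules | Block after Table 6-5 |
|---|---|---|
| Restart after Grade 3 | Resolved or Grade 1 | Grade 2 or lower |
| Grade 3 returns after restart | Permanent stop | Repeat the procedure |
| Grade 3 at a later dose or in the 24 hours following it | Permanent stop | Repeat the procedure |
| Grade 3 reactions at permanent stop | 2, under the conditions in the two rows above | 3 |
| Grade 4 | Permanent stop | Permanent stop |

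The restart threshold differs by one grade. The stop count differs by 3 − 2 = 1 reaction, which means one further exposure. The Grade 4 rule is the same in both. The later block does not mention the separate stops for laryngeal edema and bronchospasm; that silence does not cancel them and is not counted as a contradiction.

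**Step 3: where the block comes from.** It halves and then escalates an infusion rate and cites Table 6-1, which lists dilution volumes and rates in mL/hour. By content it is IV text.

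**Step 4: whether the document marks it as such.** It does not.
- The withdrawal note stands on the heading of Section 6.3.4 only.
- The block follows Table 6-5, to which the subcutaneous dose-delay text refers, and lies in the part of the protocol to which Section 6.3.5.1 sends subcutaneous users.
- It opens with the term infusion-related reaction, which Section 6.5.1.1 defines as a systemic reaction to daratumumab with no limit by route. The subcutaneous rules use the same term.
- The word infusion does not reliably signal IV. Section 6.3.3 uses it for the daratumumab dose in weeks of injection, and Section 6.3.5 speaks of post-infusion medication for subcutaneous patients.
- The third-occurrence stop names daratumumab without a route. Neither it nor the restart grade needs an mL/hour rate to be applied.

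**The case against.** The strongest reply is that rules for two routes, one of them withdrawn, do not give one patient conflicting orders. The block limits itself by its content: a rate to halve and an escalation table mean nothing for a 15 mL push over 3 to 5 minutes, and the reference to Table 6-1 leads into a section headed as discontinued. The subcutaneous rules come first, carry their own headings, name the product and say must. The restart clause in the block is only permissive, so a site that waits for Grade 1 complies with both texts. The loose uses of infusion in Sections 6.3.3 and 6.3.5 are not reaction-management rules.

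Much of this stands. The block is an IV remnant, the subcutaneous rules govern, and on restart the difference is one of permission. The practical effect is also small. Section 6.3.5 says that all patients are switching from IV and that there are no new starts. Section 1.6.1 reports, from an earlier single-agent study, that infusion-related events came predominantly with the first full infusion.

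The objection does not remove the difference in the stop rule. On a second qualifying Grade 3 reaction one text requires a permanent stop and the other sends the investigator back to the restart procedure. The reader has to infer from rate wording that the second text is obsolete, although the protocol labels the rest of the IV material explicitly.

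**Conclusion.** The concern holds. Section 6.5.1.1 contains obsolete IV text that contradicts the operative subcutaneous rules on two Grade 3 points: restart at Grade 2 or lower against resolution or Grade 1, and permanent stop at the third reaction against the second. The count of two applies only when Grade 3 returns after restart of the same dose, or recurs during a later dose or in the 24 hours after it. The restart comparison excludes laryngeal edema and bronchospasm, which have their own rules.

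This is a drafting inconsistency in a safety rule and should be corrected. The protocol gives no reaction rate for patients switched from IV to subcutaneous dosing, so no frequency can be stated; the number affected is probably small. No efficacy result depends on it.

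**What to change.** In Section 6.5.1.1, delete the paragraph after Table 6-5 on infusion-related reactions of every grade, together with its three bullets. Alternatively, label it as IV only and discontinued with version 7, matching the heading of Section 6.3.4. Add one sentence stating that the Dara-SC rules on Grade 1 or 2, Grade 3 or higher and recurrent reactions govern all subcutaneous dosing.

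The cost is one paragraph and three bullets removed, or one label added, plus the sentence. No operative rule is lost: IV dosing is unavailable, and the Grade 4 stop is already in the subcutaneous text.

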### 6.5.1.2 Hematologic Toxicity Management for Lenalidomide and Carfilzomib

Please refer to **Table 6-6** and **Table 6-7** below for dose modifications for lenalidomide and carfilzomib regarding hematologic toxicities.

